### 4.9. Blinding

The examiner and the participating older adults will be blinded to the group allocation throughout the study. An independent operator will apply SDF or potassium nitrate solution after clinical examination. If the older adult requests the treatment history, unblinding is allowed. An unblinded research assistant will disclose treatment allocation to that older adult, who will then be excluded from the study.

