### 4.8. Randomisation, Treatment Group Allocation and Allocation Concealment

A research assistant will randomly allocate eligible older adults who have at least 1 hypersensitive tooth with an SS of 8 or more due to exposed root surface into 2 intervention groups with a block randomisation of 6 and with a 1:1 ratio. A statistician will generate a random number sequence in a computer. The 2 intervention groups are as follows:SDF (test) participants will receive topical application of 38% SDF solution on the exposed root surface of the most hypersensitive tooth every 4 weeks;Potassium nitrate (positive control) participants will receive topical application of 5% potassium nitrate solution on the exposed root surface of the most hypersensitive tooth every 4 weeks.

There will be no negative control group for ethical reasons. A research assistant will keep the random number sequence in opaque sealed envelopes and conceal the allocation sequence until interventions are assigned.

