### 4.10. Outcome Measure

The primary outcome will be the change in dentine hypersensitivity of the most hypersensitive tooth in response to compressed air blast stimuli. This will be measured as the change in SS from the baseline visit to the 8-week follow-up visit after the intervention, to evaluate the anti-hypersensitivity effect of SDF and potassium nitrate solution.

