### 4.11. Sample Size Calculation

Based on a previous clinical trial [8], we estimate that the percentage of change in SS in the test and positive control groups will be 52% and 40%, respectively, with a common standard deviation of 22% and 23%, respectively [8]. Using a power of 0.8 and a statistical significance of 0.05, the minimum number of older adults needed for the study with a dropout rate of 10% was calculated to be 148, with 74 older adults per group, which was determined via the Mann–Whitney test using the software G*Power 3.1 (Franz Faul, Kiel University, Kiel, Germany) [26].

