### 4.13. Data Analysis

We will apply the statistical software SAS for Windows (SAS Institute Inc., Cary, NC, USA) and SPSS for Windows (IBM Corporation, Armonk, NY, USA) for data analyses. The data will be assessed for a normal distribution using the Shapiro–Wilk test for normality. A chi-squared test will be used to determine the difference in distribution of gender and tooth type between the 2 groups. A Mann–Whitney U test will be used to study the pre- and post-treatment SS and the reduction in SS of the treatment group if these data are not normally distributed, whereas a t-test will be used instead if these data are normally distributed. We will report the medians and interquartile ranges for all of the continuous variables to provide information on the data distribution. All statistical tests will be 2-tailed, and the significance level will be set at 0.05. This study will use the intention-to-treat principle for analysis. However, if the number of older adults who withdraw from the study is significantly different between test and positive control groups at the 8-week follow-up visit, we will use a per-protocol approach for analysis and only older adults who have completed the 8-week follow-up will be included in the results. We will also study independent variables, such as demographic background and VPI, which may modify the treatment effect.

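### Section 4.9 drops randomised participants who ask for and learn their allocation, at odds with the intention-to-treat analysis in Section 4.13

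*Protocol article*

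**What the plan says.** Section 4.8 allocates eligible adults "into 2 intervention groups with a block randomisation of 6 and with a 1:1 ratio". A treatment history exists only after that point. Section 4.9 then allows disclosure at the participant's own wish ("If the older adult requests the treatment history, unblinding is allowed"), with no medical reason required, and states the consequence: "An unblinded research assistant will disclose treatment allocation to that older adult, who will then be excluded from the study".

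Section 4.13 says: "This study will use the intention-to-treat principle for analysis". It makes one exception. If withdrawals differ significantly between arms at week 8, "we will use a per-protocol approach for analysis and only older adults who have completed the 8-week follow-up will be included in the results". Participants unblinded on request are not mentioned there.

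The primary outcome in Section 4.10 is a self-reported sensitivity score (SS): "This will be measured as the change in SS from the baseline visit to the 8-week follow-up visit after the intervention".

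**The concern.** Intention-to-treat keeps every randomised participant in the assigned arm. Section 4.9 takes some of them out because of something that happens after allocation. The trigger is the participant's own request. Someone still in pain, or someone who noticed something about the application, may be more likely to ask. The two arms receive different agents, so the rate of asking need not be equal. If poor responders ask more often, and more often in one arm, that arm's remaining participants look better than the arm really did.

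The loss is also avoidable. These people have not refused assessment; the protocol itself ends their participation. A later analysis plan cannot recover a week-8 score that was never taken.

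**Working it through.** **1. The plan's own figure.** Section 4.11 assumes that "the percentage of change in SS in the test and positive control groups will be 52% and 40%, respectively". The SDs it gives for the two arms are 22 and 23 percentage points. Power is 0.80 and alpha 0.05, two-sided by Section 4.13.
- SD = √((22² + 23²)/2) = 22.51, and d = 12/22.51 = 0.533.
- For a Mann–Whitney test with the minimum asymptotic relative efficiency of 0.864, 65 per arm gives power 0.7998 and 66 per arm gives 0.806. So n = 66 per arm.
- With 10% dropout, 66/0.90 = 73.3, rounded up to 74 per arm and 148 in total. The stated size reproduces and is not in question.

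**2. What each reading of the exclusion implies.**
- *Removed from the analysis:* a randomised participant is left out because of a post-randomisation event. This conflicts directly with Section 4.13.
- *Participation ends, earlier data kept:* Section 4.13 can still be followed in form, but the week-8 SS is missing for everyone who asks before week 8.
- *The completers-only switch in Section 4.13:* this depends on a difference in withdrawals. The Section 4.9 exclusions happen whether or not that condition is met. If they are counted as withdrawals, they could help to trigger it.

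**3. Size under assumed request rates.** The request rates p and the correlation ρ are assumptions; the documents give neither. The model works on the percentage-change scale of Section 4.11, with no true effect (mean 46 in both arms, halfway between 52 and 40), SDs of 22 and 23, and 67 per arm (74 × 0.90 = 66.6). A participant asks when a latent normal variable, correlated ρ with poor response, falls in its top fraction p.

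The retained mean in an arm rises by ρ × SD × φ(z)/(1 − p), where z is the upper-p normal quantile and φ the normal density. For 10% versus 2% with ρ = 0.5:
- 10% arm: 0.5 × 22 × 0.1755/0.90 = 2.15
- 2% arm: 0.5 × 23 × 0.0484/0.98 = 0.57
- false difference: 2.15 − 0.57 = 1.58 points, in favour of the arm with more requests

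Simulated results with the Mann–Whitney test are below. Ranges are across repeat runs of 6,000 to 10,000 trials; the Monte Carlo error of the type I error is 0.2 to 0.3 percentage points.

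| Asked, arm A vs arm B | ρ | Formula (points) | Simulated (points) | Type I error |
|---|---|---|---|---|
| 5% vs 5% | 0.5 | −0.05 | about 0 | 5.0% |
| 5% vs 2% | 0.3 | 0.38 | 0.4 | 4.8–5.1% |
| 5% vs 2% | 0.5 | 0.63 | 0.6–0.7 | 5.3–5.8% |
| 10% vs 2% | 0.5 | 1.58 | 1.5–1.6 | 6.7–6.8% |
| 15% vs 2% | 0.5 | 2.45 | 2.5 | 8.6–9.7% |
| 10% vs 2% | 0.8 | 2.52 | 2.6 | 9–10% |

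Against the planned 12 points, 0.4 to 0.7 is 3% to 6%, and 1.5 to 2.6 is 13% to 22%. Taking both inputs at their extreme (15% versus 2%, ρ = 0.8) gives 4.83 − 0.91 = 3.9 points by the same formula. I place no weight on that case, because it needs one arm to lose more than the whole 10% dropout allowance through disclosure requests alone.

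**The case against.** The strongest reply is that Section 4.9 speaks of the study and Section 4.13 of the analysis. The unblinded person may simply stop taking part and remain in the randomised arm with a missing week-8 score, whose handling belongs in an analysis plan that is not shown. This stands in part. A reader might infer that the two sections are flatly irreconcilable, and the text does not prove that. But the milder reading is not stated either, and under it the rule still discards an outcome that could have been collected.

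A reader might also infer that the rule will bias the trial or inflate its error rate to near 10%. The documents do not support that. They give no request rate, no imbalance between arms and no link to response. The larger figures need one arm to lose its whole dropout allowance or more through requests, while the other loses almost nobody. Requests may well be rare in an 8-week trial.

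Nor is there a case on power. The 10% allowance already covers losses of this kind, provided total losses stay within it.

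Finally, keeping unblinded people in the analysis lets expectation influence a self-reported pain score, and Section 5 itself stresses blinding because of placebo effects. That is a genuine trade-off. A sensitivity analysis that blanks their later scores does reproduce the loss complained of. However, with the scores collected both analyses are possible; under the present rule only the one with missing data is.

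**Conclusion.** The point holds as a conflict between a stated exclusion rule and the stated analysis principle. The minimum consequence is an avoidable, possibly informative loss of primary outcomes; the maximum is a post-randomisation exclusion from the analysis. The size is unknown. Under the assumptions above it runs from nothing (equal rates), through under 1 point with type I error near 5% (5% versus 2%), to about 1.5 to 2.6 points with type I error of roughly 7% to 10% (10% versus 2% at correlation 0.5 or 0.8; 15% versus 2% at 0.5). All of this rests on assumed rates and correlations, and on the percentage-change scale used for the sample size. It should be fixed because the correction is nearly free and the lost scores cannot be recovered later. The evidence does not make it a must-fix.

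**What to change.** In Section 4.9, replace the final clause of the disclosure sentence with wording to this effect: *the participant stays in follow-up if willing and is analysed in the arm to which they were randomised, under the intention-to-treat principle; the date and reason of unblinding are recorded.* In Section 4.13, add a sensitivity analysis that sets any SS measured after unblinding to missing. Participants' access to their treatment history need not change.

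The cost is a small wording amendment, two extra recorded items and one further analysis. The downside is that a few self-reported scores in the primary analysis come from people who know their allocation; the sensitivity analysis shows whether that matters.

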### 4.10. Outcome Measure

The primary outcome will be the change in dentine hypersensitivity of the most hypersensitive tooth in response to compressed air blast stimuli. This will be measured as the change in SS from the baseline visit to the 8-week follow-up visit after the intervention, to evaluate the anti-hypersensitivity effect of SDF and potassium nitrate solution.

### 4.11. Sample Size Calculation

Based on a previous clinical trial [8], we estimate that the percentage of change in SS in the test and positive control groups will be 52% and 40%, respectively, with a common standard deviation of 22% and 23%, respectively [8]. Using a power of 0.8 and a statistical significance of 0.05, the minimum number of older adults needed for the study with a dropout rate of 10% was calculated to be 148, with 74 older adults per group, which was determined via the Mann–Whitney test using the software G*Power 3.1 (Franz Faul, Kiel University, Kiel, Germany) [26].

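### The primary outcome is change in SS, the sample size is for percentage change, and post-treatment SS and reduction in SS are tested unranked and unadjusted; one baseline-adjusted analysis in SS points would settle this

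*Protocol article*

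**What the plan says.** Three sections of the protocol article describe the outcome variable in different ways.

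- **4.10 Outcome Measure** sets the primary outcome: "This will be measured as the change in SS from the baseline visit to the 8-week follow-up visit after the intervention". The Discussion repeats it. No percentage is mentioned.
- **4.11 Sample Size Calculation** uses percentage change: "we estimate that the percentage of change in SS in the test and positive control groups will be 52% and 40" per cent, "with a common standard deviation of 22% and 23%, respectively". The error rates are given as "Using a power of 0.8 and a statistical significance of 0.05", and the result "with a dropout rate of 10% was calculated to be 148, with 74 older adults per group" rests on a Mann–Whitney calculation in G*Power.
- **4.13 Data Analysis** applies a Mann–Whitney U test, or a t-test if the data look normal, to "study the pre- and post-treatment SS and the reduction in SS of the treatment group". On error control it says "All statistical tests will be 2-tailed, and the significance level will be set at 0.05". It does not say which comparison is decisive. Demographics and plaque index are named as possible effect modifiers; baseline SS is not named as a covariate.

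Section 4.6 restricts baseline SS: the scale runs from 0 to 10, and people scoring below 8 are excluded.

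**The concern.** The power in 4.11 is formally stated for a variable that is neither the named outcome in 4.10 nor among those tested in 4.13. In addition, 4.13 leaves two closely related versions of the outcome side by side at the same significance level. If they disagree, this text does not say which one answers the hypothesis, except by reading back to 4.10.

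Baseline SS is measured on everyone but enters only by subtraction or, in the sizing, by division. A model with baseline SS as a covariate would make the choice between post-treatment score and change irrelevant and could add some precision. What is at stake is mainly a clear decision rule, and to a lesser degree power.

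**Working it through.** **1. Reproduce 148.** Inputs from 4.11: 52% and 40%, SDs 22% and 23%, power 0.80, alpha 0.05 (two-sided by 4.13), dropout 10%.

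- Pooled SD = √((22² + 23²)/2) = 22.5; d = 12/22.5 = 0.533.
- Mann–Whitney by the asymptotic relative efficiency (ARE) method, minimum ARE 0.864: power is 0.7998 at 65 per arm and 0.806 at 66, so 66 evaluable.
- 66/0.9 = 73.3, rounded up to 74 per arm, 148 in total. This matches exactly, so the arithmetic is right and the sized variable is percentage change.

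**2. Convert to SS points.** The article gives no SD of change in points, so I take its percentage model: proportional reduction P with the stated means and SDs, assumed unrelated to baseline B.

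- Difference in points = 0.12 × B: 0.96, 1.08 and 1.20 at B = 8, 9 and 10.
- Var(change) = E[B²]·Var(P) + Var(B)·(E[P])².
- Example, B spread evenly over 8, 9, 10 (mean 9, E[B²] = 81.67, Var(B) = 0.667):
  - SDF arm: 81.67 × 0.0484 + 0.667 × 0.2704 = 4.13.
  - Control arm: 81.67 × 0.0529 + 0.667 × 0.16 = 4.43.
  - Pooled SD = √4.28 = 2.07; d = 1.08/2.07 = 0.522.

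| Assumed shares at 8/9/10 | Difference (points) | SD | d | Power at 66, min. ARE | Power at 66, normal ARE (3/π) |
|---|---|---|---|---|---|
| 60/30/10% | 1.02 | 1.94 | 0.525 | 0.793 | 0.832 |
| equal thirds | 1.08 | 2.07 | 0.522 | 0.789 | 0.828 |
| 20/30/50% | 1.12 | 2.13 | 0.524 | 0.792 | 0.831 |

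With baseline more concentrated, d rises to about 0.528 and power to about 0.80 and 0.84. Strict 80% at minimum ARE needs 67 to 68 evaluable per arm instead of 66, which is 75 to 76 after dropout instead of 74.

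**3. Why adjustment removes the ambiguity.** If Y = a + b·arm + c·B, then Y − B = a + b·arm + (c − 1)·B. The arm coefficient b is the same whether the response is the week-8 score or the change.

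**4. Precision gained.** With baseline SD s_B, week-8 SD s_Y and correlation r:

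- Adjusted/change variance ratio = s_Y²(1 − r²)/(s_B² + s_Y² − 2r·s_B·s_Y).
- Adjusted/post-score variance ratio = 1 − r².
- Assumed: s_Y = 2.0, s_B = 0.5 to 0.8, r = 0 to 0.5. At s_B = 0.8, r = 0: 4/4.64 = 0.862. At s_B = 0.8, r = 0.4: 3.36/3.36 = 1.00.
- Range: 0.86 to 1.00 against change, 0.75 to 1.00 against the post score.
- The percentage model implies r of about 0.2. Evaluable numbers per arm at minimum ARE are then 66 adjusted, 67 to 68 for change and 68 to 69 for the post score.

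**5. Consequence of two unranked tests.** Simulation with 66 per arm, the percentage model, integer SS clipped to 0–10 and the three baseline patterns above, 4,000 trials per setting:

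- No effect: at least one of the two Mann–Whitney tests (post score, change) is significant in 6.7 to 6.9% of trials. A bivariate-normal calculation with the inputs of step 4 (r = 0 to 0.4) gives 6.1 to 6.9%.
- Planned effect: the two tests disagree in 8.0 to 8.8% of trials; other runs of the same model gave 6.8 to 8.2%. I take about 8%.
- Power for change: Mann–Whitney 0.82 to 0.83, t-test 0.84, adjusted model with robust standard errors 0.84 to 0.85. Adjustment gains about 0.01 over the t-test and 0.02 over Mann–Whitney.

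**The case against.** The case against acting is substantial, and much of it limits the point.

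- **The primary variable is named.** The reduction in SS in 4.13 is the outcome of 4.10. A reader might infer that the primary outcome is undefined, or that three versions compete. Neither follows: percentage change is not among the listed tests, and the type I error above 5% arises only if a win on either variable were accepted, which the article does not say.
- **The sample size is sound.** A reader might infer that the trial is underpowered because it was sized on another variable. Step 2 shows otherwise: the narrow baseline range makes the two scales nearly interchangeable.
- **The precision argument is weak here.** The same narrow range that makes the scales interchangeable leaves baseline SS little variance to explain. Calling the unadjusted analysis a serious waste would be wrong, since unadjusted tests are valid under randomisation. The comparison with Mann–Whitney also mixes adjustment with a change of test; against the t-test the gain is about 0.01.
- **Baseline tests.** Of gender and tooth type, 4.13 says "A chi-squared test will be used to determine the difference in distribution of gender and tooth type between the 2 groups". A reader might take these tests as a substitute for adjustment, but nothing in the text says that they are.
- **Detail may sit elsewhere.** Covariates and the ranking of supportive analyses are often left to a statistical analysis plan, which is not shown.

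The last argument does not cover the conflict between 4.10 and 4.11: the article itself fixes two different variables. Nor does it cover 4.13 placing post-treatment SS beside the primary variable at the same level.

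**Conclusion.** The inconsistency is real and moderate. The outcome is defined in points and sized in per cent, and it is tested beside an unranked companion without baseline SS as a covariate. The main benefit of correcting it is to remove a choice between two variables that would disagree in about 8% of trials under the planned effect.

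The effect on power is small, and 148 is not materially wrong. The variance gain from adjustment is 0 to 14% against the change score.

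These sizes rest on assumptions that the article cannot confirm: proportional reduction unrelated to baseline, the assumed spread of baseline over 8 to 10, a week-8 SD of 2.0 and a correlation of 0 to 0.5. The mismatch between sections depends on none of them.

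**What to change.** - **Primary analysis (4.10, 4.13):** name one. Use week-8 SS (equivalently, change) in a linear model with arm and baseline SS and robust standard errors, reported as an adjusted mean difference in SS points with a 95% CI.
- **Supportive analyses:** label the unadjusted Mann–Whitney and t-tests, and any percentage change, as supportive.
- **Sample size (4.11):** restate it in points, since adjustment alone does not resolve the percentage scale. Give a difference of about 0.96 to 1.2 points for baseline 8 to 10, an SD of about 1.9 to 2.1, and the power at 66 evaluable per arm, with the percentage model stated as an assumption.

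The cost is wording only: no further data and no change to 148. The one visible downside is that the stated power may read 0.79 rather than 0.80 if the minimum-ARE assumption is kept.

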### 4.12. Data Management

Two research assistants will enter the data collected into an Excel file (by double entry) independently, and we will then compare the data to correct errors. A statistician will inspect the data entry, data checking and analysis for this study.

### 4.13. Data Analysis

We will apply the statistical software SAS for Windows (SAS Institute Inc., Cary, NC, USA) and SPSS for Windows (IBM Corporation, Armonk, NY, USA) for data analyses. The data will be assessed for a normal distribution using the Shapiro–Wilk test for normality. A chi-squared test will be used to determine the difference in distribution of gender and tooth type between the 2 groups. A Mann–Whitney U test will be used to study the pre- and post-treatment SS and the reduction in SS of the treatment group if these data are not normally distributed, whereas a t-test will be used instead if these data are normally distributed. We will report the medians and interquartile ranges for all of the continuous variables to provide information on the data distribution. All statistical tests will be 2-tailed, and the significance level will be set at 0.05. This study will use the intention-to-treat principle for analysis. However, if the number of older adults who withdraw from the study is significantly different between test and positive control groups at the 8-week follow-up visit, we will use a per-protocol approach for analysis and only older adults who have completed the 8-week follow-up will be included in the results. We will also study independent variables, such as demographic background and VPI, which may modify the treatment effect.

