### 4.6. Baseline and Follow-Up Clinical Examinations

A trained dentist will perform baseline and follow-up clinical examinations and assessments of dentine hypersensitivity. We will collect demographic background information, such as age, sex, dietary habit and denture use. A research assistant will measure the compressed cold air pressure and temperature of all the 3-in-1 syringes to be used in the Clinical Research Centre via a digital pressure indicator (DPI 2600847b) and a thermocouple digital sensor/thermometer (KM2013c) before all baseline and follow-up clinical examinations. The acceptable ranges of compressed cold pressure and temperature are 65 to 75 psi and 18 to 24 °C, respectively [8].

A trained examiner will measure the oral hygiene status of the older adults via the visible plaque index (VPI) and will record it as 0 for the absence of plaque and 1 for the presence of plaque [22]. The trained examiner will dry and clean all tooth surfaces with a piece of gauze. Cotton rolls will isolate hypersensitive teeth due to exposed root surface. They will then be assessed for dentine hypersensitivity using compressed air delivered from a 3-in-1 syringe placed approximately 1 cm away from and perpendicular to the exposed root surface for 5 s [23]. The older adult will give a self-perceived sensitivity score (SS) from 0 to 10 to all teeth under assessment for dentine hypersensitivity [8]. An SS of 0 will indicate no discomfort, whereas an SS of 10 will indicate maximum pain causing great distress to the subject (Figure 3) [24].

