We will exclude older adults with a pre-treatment SS of less than 8 from this study. For each older adult, we will select the most hypersensitive tooth (the highest SS) due to exposed root surface for the assessment of dentine hypersensitivity in follow-up visits. A dental periodontal graduated probe at the nearest mm will measure the maximum amount of gingival recession of the selected hypersensitive tooth. The same trained examiner will perform the clinical examination and assessment of dentine hypersensitivity immediately after treatment and at 4-week and 8-week follow-up visits, using the same tools and procedures as in the baseline examination. We will re-examine 10% of the older adults later on the same day to assess the intra-examiner agreement at the baseline and follow-up examinations. To promote the follow-up rate, a research assistant will remind all older adults of their follow-up appointment schedule. If they are absent at the follow-up visit, another timeslot will be provided within the same week.

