Stimulus-based or response-based assessments can evaluate dentine hypersensitivity [27]. Stimulus-based assessment is performed via applying a stimulus in an intensity to evoke pain, and it is used to measure the pain threshold; response-based assessment is performed by subjectively evaluating the pain stimuli produced, and it is used to estimate pain severity [27]. This study aims to evaluate whether SDF can reduce dentine hypersensitivity; hence, we will utilise a response-based assessment to investigate the change in pain severity that the participants perceive. In the response-based method, the visual analogue scale, numeric rating scale, verbal descriptor scale and faces pain scale are generally used for measurement [30]. Of these, the verbal descriptor scale was recommended as the scale of choice for evaluating pain intensity among older adults [30]. The SS that we will use in this study is modified according to the verbal descriptor scale, with the addition of adjective words representing different levels of pain intensity, so as to enhance the older adults’ understanding [8]. The outcome will be the change in SS from the baseline visit to the 8-week follow-up visit.

Diet and oral hygiene practice will influence dentine hypersensitivity [12]. We will provide all participants with dietary advice and standardised oral hygiene instructions before the intervention, to avoid any modification to the outcome measure. The older adults will receive a clinical examination and compressed cold air test only. Both SDF and potassium nitrate solution have been approved as safe for clinical use, and the related procedure for clinical application is simple and non-invasive. Therefore, this study will have limited ethical concerns. 

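### A Shapiro–Wilk test on the trial data chooses the primary test, although the trial was sized on Mann–Whitney alone

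*Protocol article*

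**What the plan says.** The primary outcome is defined in section 4.10 (Outcome Measure): "This will be measured as the change in SS from the baseline visit to the 8-week follow-up visit after the intervention".

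Section 4.13 (Data Analysis) sets the rule for choosing the test. First, "The data will be assessed for a normal distribution using the Shapiro–Wilk test for normality". Then, if normality fails, "A Mann–Whitney U test will be used to study the pre- and post-treatment SS and the reduction in SS of the treatment group", "whereas a t-test will be used instead if these data are normally distributed". The section does not say which variable the gate is run on, or whether it is run pooled or by arm. Its general two-sided 0.05 level presumably applies to the gate as well.

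Section 4.11 (Sample Size Calculation) names one test only. The total of 148 is a figure "which was determined via the Mann–Whitney test using the software G*Power 3.1".

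Two facts about the score matter here. Section 4.6 gives its range: "The older adult will give a self-perceived sensitivity score (SS) from 0 to 10 to all teeth under assessment". The Discussion gives its type: "The SS that we will use in this study is modified according to the verbal descriptor scale". The figure that shows the scale is not available, and no sentence says that only whole numbers are recorded.

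**The concern.** The rule makes the primary test a function of the outcome data. The two branches answer different questions: Mann–Whitney compares the ordering of the two distributions, and the t-test compares means. What the trial will report as its primary result is therefore open until the data are in.

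This is not a detail that a condensed article leaves to an analysis plan. The article states a data-dependent rule, and a later plan would have to overturn it.

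The gate may also respond to the wrong feature. A 0–10 score in whole numbers is coarse relative to its spread, and Shapiro–Wilk can reject for that reason alone, when a t-test would be perfectly serviceable. The branch taken would then depend on how an analyst runs the gate. That leaves room to prefer one result over the other.

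**Working it through.** **1. The plan's own figure.** Inputs from section 4.11: changes of 52% and 40%, SDs of 22% and 23%, power 0.80, 10% dropout. Section 4.13 gives the two-sided 0.05 level.

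- Effect size: d = 12 / √((22² + 23²)/2) = 12 / 22.51 = 0.533.
- Mann–Whitney, by the noncentral t with n scaled by the minimum asymptotic relative efficiency of 0.864: 66 per group, power 0.806.
- Dropout: 66 / 0.90 = 73.3, so 74 per group and 148 in total. This is the stated figure. The efficiency setting is inferred from the match.
- t-test at the same inputs: 57 per group; 57 / 0.90 = 63.3, so 64 per group and 128 in total. At 66 per group its power is 0.860.

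The 148 belongs to the Mann–Whitney branch, and it is also enough for the t-test branch.

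**2. Simulation model.** Evaluable number 74 × 0.90 = 66.6, taken as 67 per arm. The percentage reduction is normal with the section 4.11 means and SDs, and the post-treatment score is limited to 0–10. The gate level is 0.05. The baseline mix of scores 8/9/10 is not in the document. It is assumed and varied from 33/33/33 to 80/15/5, with 50/30/20 in between.

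**3. How often the gate rejects normality of the reduction in SS.**

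| Scores | Arms pooled | By arm, either rejecting |
|---|---|---|
| Whole numbers | over 99% | about 76–91% |
| Same scores unrounded | about 4–6% | up to about 9% |

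For exactly normal data, two tests at 0.05 would reject at least once in 1 − 0.95² = 9.75% of trials. The unrounded results are therefore about what chance gives, and rounding produces the rest.

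A cross-check: with the 50/30/20 mix the mean baseline is 0.5×8 + 0.3×9 + 0.2×10 = 8.7, so the SD of the reduction is about 0.23 × 8.7 = 2.0 points. A plain normal with SD 2, rounded to whole numbers, is rejected in 55% of single samples of 67 and in over 99% of samples of 134. For two arms, 1 − 0.45² = 80%, in line with the table.

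**4. The result is not universal.** With SD 2.5 the rounded normal is rejected in 27% of samples of 67 and 75% of samples of 134. A by-arm gate on percentage change, the scale used for sizing, rejects in 23%.

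**5. Consequences for the test** (67 per arm, whole numbers, 50/30/20 mix, gate by arm).

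| | t-test | Mann–Whitney | Gated |
|---|---|---|---|
| Type I error | 0.046 | 0.046 | 0.047 |
| Power | 0.838 | 0.824 | 0.826 |

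The t-test and Mann–Whitney disagree on significance in about 2% of trials under the null and about 4% at the planned effect. Always reporting the smaller of the two p-values would give a type I error of about 0.056.

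**The case against.** The strongest reply is that the rule is written down, chooses between two named tests, and does no measurable harm. That largely stands. Applied consistently, it holds the error rate and the power. With whole-number scores the trial would usually end on Mann–Whitney, the test it was sized for, and the other branch needs fewer participants. A reader might infer inflated type I error or an underpowered t-test branch; the figures support neither.

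A second reply is that the rounding argument rests on something the article does not state. That also stands. A reader might take whole-number scoring as given, but the wording supports it only by implication. The simulation also assumes a normal underlying reduction. Real scores that start at 8 or more and stop at 0 could be truly skewed, and the gate would then detect a real departure. So the claim that the gate detects only rounding holds under those assumptions and not in general.

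Third, a reader might argue that baseline SS can never look normal, so the t-test branch is unreachable. Section 4.6 does restrict entry ("We will exclude older adults with a pre-treatment SS of less than 8 from this study"), and that truncation makes baseline scores non-normal even without rounding. But baseline SS is not the primary outcome, and the ordinary reading of section 4.13 is that each variable is checked on its own.

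None of these replies names the primary test in advance.

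**Conclusion.** The point holds as one of prespecification. Section 4.13 lets the trial data select the primary test and with it the quantity being compared, although section 4.11 had already settled on Mann–Whitney for design.

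The size is modest. The choice of branch would change the significance call in about 4% of trials at the planned effect and 2% under the null. Power under the gate stays within about 2 points of either fixed test. Error inflation, to about 0.056, arises only if the gate is bypassed and the better of the two results is reported.

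The rejection rates rest on whole-number scoring, a normal underlying percentage reduction, the planning values of section 4.11 and an assumed baseline mix. The lack of a fixed primary test rests on the text alone. The change is worth making because it is cheap, not because the present rule would invalidate the trial.

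**What to change.** In section 4.13, delete the Shapiro–Wilk gate and the either/or rule, and name one primary test for the change in SS from baseline to 8 weeks, to be used whatever the distribution.

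- Mann–Whitney is the direct choice: it is the test behind section 4.11 and leaves the total at 148.
- A baseline-adjusted linear model with robust standard errors, fixed in advance, is an acceptable alternative with similar power. It is a preference and is not required by the defect.

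Report the analysis not chosen as a sensitivity analysis, and look at distributional shape by plots only.

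Cost: one sentence changed and one additional sensitivity analysis, with no change in sample size.
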